### Elimination criteria

Patients with cerebral infarction, cerebral hemorrhage, or other brain tumors diagnosed on the basis of skull computed tomography or MRI and patients who refuse to sign the written informed consent or did not coordinate with the randomized enrollment will be excluded from the study.

### Randomization

Patients will be randomly assigned to one of the four treatment groups. Computerized randomization will be performed by an investigator who has no direct contact with the participants. The assessors will be blinded to the group allocation. The investigator performing the acupuncture intervention will not be intrinsically blinded; however, the investigator will not be allowed to communicate with the participants or the assessors about the treatment procedures and outcomes. A sealed envelope containing an allocation sequence number for each patient will be opened right after each patient is verified to meet the eligibility criteria and has signed the informed consent form. If any error or disclosure with regard to randomization occurs, a new randomization sequence will be generated starting from the problematic serial number and applied to subsequent patients.

### Interventions

#### Acupuncture therapy

Acupuncture will be performed by specialists in traditional Chinese medicine, and the protocol will follow the details of the Standards for Reporting Interventions in Clinical Trials for Acupuncture 2010 checklist [22, 23], as shown in Table 1.

**Table 1 Tab1:** Details of acupuncture intervention

		Description
Acupuncture rationale	Style of acupuncture	Traditional Chinese medicine
	Rationale for treatment	Acupuncture has been historically used to treat facial palsy. Additionally, it is known to be a safe treatment used in a wide range of symptoms caused by Bell’s palsy
	Extent to which treatment varied	The subjects of the intervention group all receive the same acupuncture or electroacupuncture treatment
Details of needling	Number of needle insertions per subject per session	10
	Names of the insertion points (uni- or bilateral)	GB14, TE23, Qianzheng, LI20, SI18, ST4 (unilateral, affected side), LI4, LR3 (bilateral)
	Depth of insertion	10–30 mm (exact depth shown in Table 2)
	Response sought	*Deqi*
	Needle stimulation	Some in electric stimulation, others in manual stimulation (exact details are in the text)
	Needle retention time	20 minutes
	Needle type	0.30 mm (diameter) × 25 mm (length) disposal needle (Huatuo Acupuncture, Suzhou, China)
Treatment regimen	Number of treatment sessions	12
	Frequency and duration of treatment sessions	3 sessions/wk for 4 wk
Other components of treatment	Details of other interventions administered to the acupuncture group	No other interventions
	Setting and context of treatment	All subjects are informed that they will receive acupuncture or electroacupuncture treatment, which can potentially reduce Bell’s palsy symptoms; however, the non-acupuncture control group would have to complete the evaluations during the first week before receiving the same treatment as the acupuncture group.
Practitioner background	Description of participating acupuncturists	Specialists in traditional Chinese medicine with at least 3 years of practice in acupuncture
Control or comparator interventions	Rationale for the control or comparator in the context of the research question	Non-acupuncture control is used as a control because sham acupuncture cannot be a substituted for a physiologically inert placebo, and Western medicine is recommended in the guideline.
	Precise description of the control or comparator	The Western medicine control group forms a positive control and completes the evaluations during the first week after randomization.

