**Methods/Design:**

A total of 132 patients with Bell’s palsy (grades III and IV in the House-Brackmann [HB] Facial Nerve Grading System) will be randomly divided into electroacupuncture, manual acupuncture, non-acupuncture, and medicine control groups. All the patients will be given electroacupuncture treatment after the acute period, except for patients in the medicine control group. The acupuncture or electroacupuncture treatments will be performed every 2 days until the patients recover or withdraw from the study. The primary outcome is analysis based on facial nerve functional scales (HB scale and Sunnybrook facial grading system), and the secondary outcome is analysis based on MRI, nerve electromyography and F-wave detection. All the patients will undergo MRI within 3 days after Bell’s palsy onset for observation of the signal intensity and facial nerve swelling of the unaffected and affected sides. They will also undergo facial nerve electromyography and F-wave detection within 1 week after onset of Bell’s palsy. Nerve function will be evaluated using the HB scale and Sunnybrook facial grading system at each hospital visit for treatment until the end of the study. The MRI, nerve electromyography, and F-wave detection will be performed again at 1 month after the onset of Bell’s palsy.

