### Western medicine treatment

Patients in each group will be given oral administration of prednisone (30 mg once daily for 5 days and then 5 mg daily until study withdrawal), mecobalamin (0.5 mg thrice daily), and fursutiamine (50 mg thrice daily) until complete recovery. Group D serves as the medicine control group, which will not be given any acupuncture or electroacupuncture therapy throughout the trial.

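### Table 1 says every subject is told they will receive acupuncture or electroacupuncture, but group D (33 of 132) never receives either

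*Protocol article*

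**What the plan says.** The row of Table 1 on setting and context of treatment (Protocol article, Acupuncture therapy) reads "All subjects are informed that they will receive acupuncture or electroacupuncture treatment". It adds that this treatment may reduce symptoms, then makes one qualification: "the non-acupuncture control group would have to complete the evaluations during the first week before receiving the same treatment as the acupuncture group". That describes group C, which starts after the acute stage.

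The Western medicine treatment section describes group D as the medicine control group, "which will not be given any acupuncture or electroacupuncture therapy throughout the trial". The abstract agrees: "All the patients will be given electroacupuncture treatment after the acute period, except for patients in the medicine control group".

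On allocation, the Randomization section says "Patients will be randomly assigned to one of the four treatment groups", and that a sealed envelope "will be opened right after each patient is verified to meet the eligibility criteria and has signed the informed consent form". It also says "The assessors will be blinded to the group allocation". No blinding of patients is described. Under Elimination criteria, patients who refuse to sign consent or who "did not coordinate with the randomized enrollment will be excluded from the study".

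**The concern.** The Table 1 statement admits immediate acupuncture (groups A and B) and delayed acupuncture (group C). It has no place for a group that gets none. All four groups are drawn from one randomised pool, and nobody's group is known when consent is signed. A statement made to everyone at that point would also reach the patients who later draw D.

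A patient led to expect acupuncture who then draws D has a reason to refuse, withdraw or seek acupuncture elsewhere. Patients in A to C have no such reason, although C must wait. The elimination rule does not say whether it applies before or after the envelope is opened. If it is applied afterwards, a patient who declines D could be removed from the study. The arm would then be left with those willing to go without acupuncture.

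This matters because D is the only arm without acupuncture throughout, so only comparisons with D can show what acupuncture adds to medicine. Losses from D that are related to patients' expectations would bias those comparisons. The per-protocol analysis is most exposed. The intention-to-treat analysis is exposed too if excluded patients are not counted.

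**Working it through.** **1. What Table 1 would tell each group, against what the group receives**

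| Group | Acute stage | After the acute stage | Is the Table 1 statement true? |
|---|---|---|---|
| A | Electroacupuncture | Electroacupuncture | Yes |
| B | Manual acupuncture | Electroacupuncture | Yes |
| C | None | Electroacupuncture | Yes, with the stated delay |
| D | None | None | No |

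The treatments come from the sections Acute stage, Stable and recovery stages, and Western medicine treatment.

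**2. Does "All subjects are informed that they will receive acupuncture or electroacupuncture treatment" perhaps mean groups A to C only?** Three features of the table count against this. Where it means a subset, in the row on how far treatment varied, it refers to the intervention group's subjects. Its comparator rows cover the Western medicine control group, so D is not outside its scope. The sentence itself makes an exception for C and none for D.

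**3. Number of patients affected.** The Sample size calculation gives 33 per group and 132 in total.
- 132 / 4 = 33 patients in D
- 33 / 132 = 25%

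**4. The plan's own sample size.** Formula: n = (1.96 + 1.28)² × (σ₁² + σ₂²) / δ².
- Sunnybrook: 10.4976 × (10² + 18²) / 13² = 26.34 (stated: 26.33)
- HB: 10.4976 × (1² + 3²) / 2² = 26.24 (stated: 26)

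Both round up to the stated 27 per group. The 33 enrolled per group follows from 27 × 1.2 = 32.4. Dividing by the retained fraction, 27 / (1 − 0.2), would give 34 per group and 136 in total, but the present point does not depend on that. The 20% allowance is a single rate for all groups: 0.2 × 33 = 6.6 patients per group.

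**5. Would extra loss from D matter through power?** The documents give no dropout figure specific to D, so the range below is an assumption. The other arm keeps 33 × 0.8 = 26.4 evaluable patients, and D keeps 33 × (1 − d). Power = Φ(δ / SE − 1.96), with SE = √(σ_treatment² / 26.4 + σ_control² / n_D).

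| Assumed dropout in D | Evaluable in D | Sunnybrook power | HB power |
|---|---|---|---|
| 20% | 26.4 | 90.0% | 90.1% |
| 30% | 23.1 | 89.1% | 89.7% |
| 40% | 19.8 | 87.8% | 89.2% |
| 50% | 16.5 | 85.9% | 88.4% |

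Worked case for Sunnybrook at 40%: SE = √(324 / 26.4 + 100 / 19.8) = √17.32 = 4.162; 13 / 4.162 − 1.96 = 1.163; Φ(1.163) = 87.8%.

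Power falls little because the plan gives the control arm the smaller standard deviation. What remains is the question of who leaves, and these figures cannot measure that.

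**The case against.** The best defence is that the row is loosely worded and nothing more. Table 1 is headed as details of the acupuncture intervention and follows an acupuncture reporting checklist. It is imprecise elsewhere: it records no other interventions for the acupuncture group, although every group also receives oral medicine. The sentence covers exactly immediate and delayed acupuncture, which are groups A to C. The row also does not say when subjects are informed. If they are told after allocation, and only those who will be needled, nothing untrue is said to D. This reading is possible, but the table's wording makes it weak (step 2). Even if it is right, the sentence as written is wrong and needs correcting.

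It is also true that nothing in the documents reports or predicts higher refusal or withdrawal in D. D patients receive active medicine, the assessors are blinded, scores are averaged over three physicians, and an intention-to-treat analysis is planned. These measures limit rating bias, but they do not prevent patients from leaving. The elimination rule may already be meant to screen out those who will not accept randomisation. It does not say that this happens before the envelope is opened.

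Two stronger readings might be inferred, and neither is supported. One is that consent from group D is invalid. The consent form is not shown, the article states that written consent is obtained and that an ethics committee approved the study, and the timing of the Table 1 statement is unknown. The other is that rewording would remove expectation bias. Patients in D know that they receive no needles whatever the information sheet says, so open allocation leaves that bias in place.

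**Conclusion.** The contradiction is real and stands in the current text. Table 1 says all subjects are told they will receive acupuncture or electroacupuncture, while the abstract and the Western medicine treatment section say that group D receives neither. By design this concerns 33 of 132 patients (25%).

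That patients actually receive untrue information depends on one condition: that they are informed as Table 1 says, before allocation. Given that, selective refusal or withdrawal from D is plausible. It is not documented, and its size cannot be estimated from the article. The effect on power would be small even at twice the planned dropout, so the reason to act is possible bias in the comparisons with D and the accuracy of what patients are told.

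**What to change.** - Reconcile Table 1 with the abstract and the Western medicine treatment section. The row should say that all candidates are told before consent that there are four groups, that one in four receives medicine without acupuncture throughout, and that one in four starts acupuncture only after the acute stage.
- Check that the patient information sheet says the same.
- Confirm and record, before the envelope is opened, that the patient accepts any of the four groups.
- Removing the remark that the treatment may reduce symptoms is optional. It is hedged and not in itself untrue.

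No sample size changes. The ethics committee must be notified, and a few patients who insist on acupuncture will decline before randomisation. Recruitment began in January 2015 (Trial status). If the information sheet proves to match Table 1, the notification should therefore also cover patients already enrolled. If the sheet already describes all four groups, the change to the patient information reduces to correcting the table.

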### Acute stage

Patients in groups A and B will receive acupuncture therapy at the Cuanzhu (BL2), Yangbai (GB14), Sizhukong (TE23), Qianzheng, Yingxiang (LI20), Quanliao (SI18), Dicang (ST4), Hegu (LI4), and Taichong (LR3) points. The acupuncture points are identified according to the method of point location issued by the World Health Organization (WHO). The acupuncture needles will be inserted straightly or obliquely with a depth of 10–30 mm to bring about the desired sensation of *deqi* (see Table 2), and the needles will be left in place for 20 minutes. The acupuncture therapy will be performed once every 2 days. Accordingly, patients in group A (electroacupuncture in the acute stage) will receive electroacupuncture therapy at the Yangbai (GB14)-Sizhukong (TE23), Quanliao (SI18)-Yingxiang (LI20), and Qianzheng-Dicang (ST4) points (2 Hz, density wave, 20 minutes) once every 2 days. Patients in group C will not receive acupuncture therapy.

**Table 2 Tab2:** Acupuncture points and needle insertion procedures

Acupuncture point	Direction	Depth (mm)
GB14 (yangbai, affected side)	Transversely toward geisoma	20–30
SJ23 (sizhukong, affected side)	Obliquely toward partes temporalis	20–30
Qianzheng (extra point, affected side)	Perpendicular to the skin	20–30
LI20 (yingxiang, affected side)	Obliquely along nasolabial sulcus toward the root of the nose	20–30
SI18 (quanliao, affected side)	Perpendicular to the skin	20–30
ST4 (dicang, affected side)	Transversely toward ST6	10–20
LI4 (hegu, bilateral)	Perpendicular to the skin	20–30
LR3 (taichong, bilateral)	Perpendicular to the skin	20–30

### Stable and recovery stages

Patients in groups A–C will receive straight or oblique acupuncture with a depth of 10–30 mm at the Cuanzhu (BL2), Yangbai (GB14), Sizhukong (TE23), Qianzheng, Yingxiang (LI20), Quanliao (SI18), Dicang (ST4), Hegu (LI4), and Taichong (LR3) points (identified according to the method of point location issued by the WHO) to bring out the desired sensation of *deqi* from the eighth day after palsy onset. The needles will be retained for 20 minutes. The electroacupuncture will be performed once every 2 days. Accordingly, patients in groups A–C will receive electroacupuncture therapy at the Yangbai (GB14)-Sizhukong (TE23), Quanliao (SI18)-Yingxiang (LI20), and Qianzheng-Dicang (ST4) points (2 Hz, density wave, 20 minutes). All patients will be given therapies until the endpoint of complete recovery or study withdrawal.

### Western medicine treatment

Patients in each group will be given oral administration of prednisone (30 mg once daily for 5 days and then 5 mg daily until study withdrawal), mecobalamin (0.5 mg thrice daily), and fursutiamine (50 mg thrice daily) until complete recovery. Group D serves as the medicine control group, which will not be given any acupuncture or electroacupuncture therapy throughout the trial.

### Outcome

To reduce the outcome assessment bias, the investigators will be given specific training for facial grading, and both the Sunnybrook and HB scales will be used for outcome evaluation.

### Primary outcome

Evaluation will be performed using facial paralysis evaluation scale (HB and Sunnybrook scales). Measurements will be performed at the above-mentioned time points and at the first month after therapy by three physicians, and the averaged value will be recorded. Meanwhile, the time for the first change in the score after the start of treatment will be labeled. The period from palsy onset to the first change in the facial paralysis evaluation scale score and the patient’s overall recovery period will be recorded, and comparison between the interventional groups and the control group will be conducted.

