## Background

Acupuncture therapy is widely used for the treatment of Bell’s palsy in China and throughout the world [1–4]; however, its effectiveness is still debatable because conclusions drawn from Cochrane reviews [5, 6] and meta-analyses [7, 8] do not support its clinical application, whereas clinical trials tend to prove its efficacy [9, 10]. Except for some defects in the protocol design and implementation, different manipulations among Chinese and foreign physicians, and the lack of powerful evidence of objective detection and assessment besides the neurological function scale, are very important reasons for the conflicting opinions.

The detectable pathological changes of peripheral facial paralysis (including Bell’s palsy) are facial nerve edema and bioelectric conduction disorders. The former can be detected and evaluated using magnetic resonance imaging (MRI) [11–15], the latter using more sensitive neural electrophysiological methods [16].

Treatments for Bell’s palsy should differ according to the stage of the disease [17], and the most important factor in treatment is not the kind of manipulation but when to initiate the intervention, with the goal being to start in the acute stage within 7 days of palsy onset [18–20]. Currently, electroacupuncture is widely used in the treatment of Bell’s palsy, although there is inadequate evidence-based support, especially for use in the acute stage. On the one hand, some clinical experiences have revealed that an early and appropriate electroacupuncture therapy shortens the disease course and improves the curative effect [9, 21]. On the other hand, there are beliefs that electroacupuncture stimulation is not appropriate for patients in the acute stage of Bell’s palsy and that it is more likely to aggravate facial nerve edema and bioelectric conduction disorders. Thus, the efficacy of electroacupuncture for treating Bell’s palsy starting from the acute stage is yet to be investigated.

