### Inclusion criteria

Patients with Bell’s palsy who meet the following inclusion criteria will be enrolled in the study: unilateral facial paralysis; age between 18 and 60 years; Bell’s palsy onset within 2 days; HB scale score above grade III; normal superficial and deep sensations, muscle strength and muscle tension in limbs, with negative pathological signs; and absence of heart failure, abnormal liver function, and other severe complications of diabetes mellitus.

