### Statistical analysis

In this study, statistical analyses of data will be performed by professionals rather than investigators using intention-to-treat and per-protocol approaches. All demographic and clinical characteristics of the subjects (such as sex, age) will be processed based on descriptive analyses. Quantitative data will be presented as average, standard deviation, median value, and range. Qualitative data will be presented as the frequency and percentage.

For the primary outcome measurements, a repeated-measures multifactorial analysis will be performed to identify differences between groups (differences within each group based on time, and the effects of the interaction of the variables based on group) to compare the differences in HB and Sunnybrook score changes between the interventional and control groups based on time (baseline, every treatment time and 1 month after palsy onset). The period from the onset to the first change in facial paralysis evaluation scale score in and the patients’ overall recovery period will be compared using one-way analysis of variance (ANOVA) between all groups. For the secondary outcome measurements, a χ^2^ test will be used to compare the edema onset frequency of the facial nerve on the affected side. One-way ANOVA will be applied to identify differences in results of facial nerve electromyography and F-wave detection between groups. In cases of non-normally distributed data, the Kruskal-Wallis H test will be performed.

All adverse events reported during the study will be included in the clinical report, and the prevalence of adverse events will then be calculated. The percentage of participants with adverse events in each group will be calculated and compared using the χ^2^ test or Fisher’s exact test. Statistical analyses will be performed using IBM SPSS for Windows version 19.0 statistical software (IBM, Armonk, NY, USA). All the tests will be two-sided, and a *P* value <0.05 will be considered statistically significant.

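### Time to first change counts a change in either direction and of any size, so a shorter time cannot be read as benefit

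*Protocol article*

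**What the plan says.** The Primary outcome section of the protocol article names two scales, HB and Sunnybrook, scored "by three physicians, and the averaged value will be recorded". It then adds a time measure: "the time for the first change in the score after the start of treatment will be labeled", with the recorded variable being "The period from palsy onset to the first change in the facial paralysis evaluation scale score". The overall recovery period is recorded beside it.

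The Statistical analysis section repeats the event in the same form: "The period from the onset to the first change in facial paralysis evaluation scale score in and the patients’ overall recovery period will be compared" between all groups by one-way ANOVA. The same section gives the HB and Sunnybrook score changes a separate repeated-measures analysis.

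On timing, the Abstract has both scales scored at every treatment visit for as long as the trial runs. Acupuncture treatment is every 2 days. The Inclusion criteria require "onset within 2 days". The Background reports a belief that electroacupuncture in the acute stage is unsuitable because "it is more likely to aggravate facial nerve edema and bioelectric conduction disorders".

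**The concern.** As written, the event is any difference between a later score and the starting score. Three things are left open: whether the score must improve, by how much, and on which of the two scales.

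Two kinds of unwanted event follow. A patient who gets worse in the first days has an early event and a short time. So does a patient whose condition has not moved but whose averaged score differs by a third of a unit because one physician scored one unit differently. Neither is distinguished from a patient who starts to recover.

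The measure sits under the primary outcome and has its own between-group test, so a significant result would probably be reported as faster response. Whether acute-stage electroacupuncture helps or aggravates is the question the trial sets out to examine, and an endpoint that gives the same answer in both cases does not help to decide it.

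**Working it through.** **The article's own figures.** No figure in the article describes rater error or sizes this time variable. The Sample size calculation concerns score change. With its z-values, (1.96 + 1.28)² × (10² + 18²) / 13² = 26.34 for Sunnybrook and (1.96 + 1.28)² × (1² + 3²) / 2² = 26.24 for HB, so its 27 per group reproduces. The 13 and 2 points there are between-group differences in change, not thresholds for one patient's event.

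**Assumptions.** Whole-unit ratings, errors independent between physicians and visits, a true score on a whole number, and a mean of three stored unrounded. The rater SD s is assumed and varied.

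**Chance that an unchanged patient shows a change between two assessments, Sunnybrook.** The SD of the difference between two three-physician means is s × √(2/3): 0.82 for s = 1 and 2.45 for s = 3. The mean moves in steps of 1/3, so for s of 1 or more

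P(exactly equal) ≈ (1/3) / (SD × √(2π)) = 0.163 for s = 1 and 0.054 for s = 3,

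which gives about 84% and 95% for a non-zero change. Below s = 1 this approximation is poor, so simulation (200,000 patients) is used throughout:

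| Rater SD (points) | Mean of three physicians | Single physician |
|---|---|---|
| 0.25 | 23% | 9% |
| 0.5 | 71% | 48% |
| 1 | 84% | 73% |
| 3 | 95% | 91% |

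About half of these changes are worsenings. Averaging makes the noise smaller, but it also makes an exact tie rarer.

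**The same for HB.** Each physician is assumed to be off by one grade, in either direction, with probability q. For q = 0.05, the chance that at least one of six ratings is off is 1 − 0.95⁶ = 0.265. The chance that exactly two are off and cancel is 15 × 2 × 0.025² × 0.95⁴ = 0.015. This leaves 0.25, as simulated. For q = 0.05, 0.10 and 0.20 the simulation gives 25%, 42% and 61%, against 10%, 19% and 34% for one physician.

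**Can a worsening arm look faster?** Assumed example: 33 patients per arm, scored every 2 days from day 2. One arm loses 1 or 2 Sunnybrook points per day to day 8 while the other is flat; both then gain 2 points per day. There were 300 simulated trials per setting, with a two-arm t-test.

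| Rater SD | Mean time to any change, worsening arm vs flat arm (days) | Trials with p < 0.05 |
|---|---|---|
| 0 | 4.0 vs 10.0 | 100% (no spread within arms) |
| 0.25 | 4.0 vs about 8.0 | 100% |
| 0.5 | 4.0 vs 4.8 | 99% |
| 1 | 4.0 vs 4.4 | 56–72% |
| 3 | 4.0–4.1 vs 4.1 | 3–6% |
| 5 | 4.0–4.1 vs 4.1 | 1–2% |

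Up to SD 1 the worsening arm appears faster. At SD 3 to 5 nearly everyone has changed by the second assessment, and the measure says almost nothing. With a directional event (at least 13 points better, chosen only for illustration and without confirmation) the order is right at every noise level: about 18 to 22 days in the worsening arm against 15 to 16.

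**The case against.** The strongest reply is that this is one component among several. The repeated-measures analysis compares HB and Sunnybrook score changes over time and keeps their sign, and the sample size rests on score change. Worsening in any arm would show in the serial scores, and adverse events are compared by group. This stands. A reader might infer that the primary comparison as a whole is compromised; the article does not support that.

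A second reply is that the phrase, placed beside overall recovery, naturally means first improvement, and that thresholds belong in a fuller document. The intention may well be improvement, and the exact threshold can fairly be left elsewhere. But the article states the event twice and attaches a test to it, each time without direction. Followed as written, the rule counts worsening.

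A third reply concerns size. Rater error is assumed throughout, raters are trained (Outcome section) and assessors are blinded (Randomization section). This also stands. The false-change probability depends strongly on the assumed error, and it does not measure the risk of reversal. Reversal needs real early worsening and fades as noise grows.

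Two further inferences should be resisted. The Background reports beliefs about nerve edema and conduction, not about falling facial scores, so the article does not predict worsening on these scales in group A. It might also seem that groups A and B would look faster merely because they attend more often in the first week. Table 1 says that the control groups complete evaluations in that week but not how often, so this cannot be established.

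**Conclusion.** The point holds for the time-to-first-change component only. Its definition treats improvement, worsening and a one-third-unit rater fluctuation alike, so a shorter time has no clear meaning. That conclusion follows from the wording and needs no assumption.

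The size does need assumptions. Over rater SDs of 0.25 to 3 Sunnybrook points, a false change at the second assessment has probability of roughly 23% to 95%. The apparent advantage of an arm that worsens early is a possibility under low rater noise and an assumed early decline, not an expected result of this trial. This should be corrected, but it does not undermine the trial's main score comparison.

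**What to change.** In both the Primary outcome and Statistical analysis sections, replace the event with time to first improvement from baseline, stating:

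- the scale that defines it, and which direction on that scale is improvement;
- a prespecified minimum improvement in the averaged score, larger than rater error. One full HB grade would be an illustration; the investigators should choose the value, and the planned rater training is an opportunity to measure the error;
- confirmation at the next scheduled assessment, with the event dated at the first of the two;
- how a patient who never meets the definition is handled.

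Report early worsening by arm as a separate result.

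The same ratings serve, so no new data collection is needed. The small downside is that each event needs one further assessment before it counts.
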